##### Secondary outcomes

1. Neurocognitive function [validated MoCA for the Sri Lankan population—the Sinhala version of the Montreal Cognitive Assessment (MoCA-S) was validated and published in 2011 as a screening instrument for dementia in Sri Lanka]. 2. Neurophysiological functions—peripheral nerve conduction (upper and lower limb nerves). 3. Brain electrical activity (EEG). EEG data will be collected at baseline, at mid-point and follow-up visits to assess neurophysiological changes associated with aging. Resting-state EEG recordings will be obtained with participants seated comfortably, using a 64-channel cap following the 10–20 system. Participants will undergo 5-min recordings with eyes open and eyes closed. The raw EEG data will be preprocessed by applying band-pass filtering (0.5–45 Hz), notch filtering at 50/60 Hz, and artifact removal through automated detection, manual review, and independent component analysis to eliminate eye blinks, muscle activity, and other noise. Key parameters such as spectral power in delta, theta, alpha, beta, and gamma bands, peak frequency, and measures of signal complexity will be extracted. Connectivity analyses, including coherence and phase lag indices, will also be performed. These neurophysiological metrics will be analyzed to evaluate age-related brain changes and their association with clinical outcomes. 4. Assess health-related quality of life (HRQoL) using a validated questionnaire and Health-related quality of life (HRQoL) measured using an HRQoL questionnaire (52).

### Safety assessment

Each participant will undergo hematological and biochemical assessments, including fasting blood sugar (FBS), full blood count (FBC), erythrocyte sedimentation rate (ESR), aspartate aminotransferase (AST), alanine aminotransferase (ALT), and serum creatinine/glomerular filtration rate (GFR), along with a comprehensive urine analysis, both before and after the intervention. These evaluations primarily serve as a safety assessment measure. Adverse events experienced by participants will be systematically recorded on a weekly basis by investigators during scheduled visits to the clinical trial center. Additionally, participants will be instructed to document any adverse reactions in their diaries and promptly report them using the designated contact numbers. In the event of unexpected symptoms or concerns, they will be advised to visit the trial center at the Faculty of Indigenous Medicine for further evaluation. Any serious adverse events will undergo thorough assessment and will be reported to the Ethics Review Committee (ERC) of the Faculty of Indigenous Medicine within five working days. Although no severe adverse reactions are anticipated with BMFD Herbal supplement, in cases where an adverse reaction necessitates hospitalization, appropriate medical care and expert management will be ensured. If at any point the safety of trial participants can no longer be guaranteed or new scientific evidence emerges indicating potential risks, the clinical trial will be prematurely terminated.

#### Safety monitoring and stopping criteria

Participants will be monitored for adverse events throughout the study period. Predefined laboratory thresholds for discontinuation include elevations of liver enzymes (ALT or AST > 3× upper limit of normal), serum creatinine >1.5× baseline, or any laboratory abnormality graded ≥3 according to CTCAE criteria. Occurrence of any serious adverse event deemed related to the intervention will result in immediate discontinuation of the study product for that participant. The trial will be temporarily suspended if two or more participants experience unexpected serious adverse events related to the intervention, pending safety review.

### Blinding procedure

To ensure double blinding, an independent staff member (unblinded dispenser), who is not involved in participant recruitment, outcome assessment, or data analysis, will be responsible for labeling, coding, and dispensing either BMFD or placebo sachets according to the randomization schedule. The PI, investigators, outcome assessors, and participants will remain blinded to group allocation until completion of the trial. Emergency unblinding will be permitted only if medically necessary.

### Outcome assessor blinding

All primary and secondary outcomes will be measured in both the BMFD and placebo groups using standardized procedures.

Primary outcomes (telomerase activity and telomere length) will be measured using laboratory assays with coded samples, ensuring objective assessment and minimizing bias.

Secondary outcomes [cognitive function, neurophysiological function, and health-related quality of life (HRQoL)] will be administered identically to both groups. Where feasible, scoring of subjective outcomes will be performed by assessors blinded to group allocation to reduce potential measurement bias (see Table 2).

**Table 2 tab2:** Study procedures.

Study procedures/assessments	Screening (Week 1)	Baseline (Week 0)	Week 6	Week 12 (Endline)
Enrollment				
Eligibility screening	✓			
Informed consent	✓			
Recruitment	✓			
Randomization		✓		
Interventions				
ARM 1: BMFD administration		✓	✓	✓
ARM 2: Placebo administration		✓	✓	✓
Assessments/investigations				
MoCA (cognitive assessment)		✓	✓	✓
Constitutional (*Prakriti*) analysis		✓		
Nerve conduction test (NCT)		✓		✓
Electroencephalography (EEG)		✓		✓
Telomere length		✓		✓
Telomerase activity		✓		✓
Health-related quality of life (HRQoL)		✓	✓	✓
Safety monitoring				
Adverse event assessment		✓	✓	✓

✓ indicates the procedure performed at the specified timepoint.

Baseline = prior to initiation of intervention.

Week 12 represents end-of-treatment follow-up.

HRQoL—health-related quality of life.

### Data handling, record keeping, and dissemination

Each participant will have an individual file to securely store hard copies of case record forms, including informed consent, results from hematological and biochemical investigations, physical examination findings, completed questionnaires, NCT and EEG Data, Moca test data and QPCR analysis data. Data entry will be performed by a limited number of dedicated staff members and saved on a password-protected, dedicated computer. These data will remain with the researchers and will not be shared with any third party under any circumstances. Participant information will be securely stored during each clinic visit throughout the study. Upon study completion, all records will be securely retained for a period of 10 years. Participant data will be stored at the Department of Basic Principles, Ayurveda Anatomy, and Physiology, Faculty of Indigenous Medicine, University of Colombo. These data will be used exclusively for statistical analysis and scientific reporting. Identifying information, such as contact details, will be stored separately from research data. Each participant and their corresponding data will be assigned a unique study identification number. After the study concludes, all databases will be de-identified and archived. A Data Safety Monitoring Board, composed of three independent experts, has been appointed in accordance with the guidelines set by the Ethics Review Committee of the Faculty of Indigenous Medicine to ensure safety monitoring. As this is a single-center trial involving only 74 participants, no audit is planned for this study. The study results will be disseminated through scientific conferences and peer-reviewed journals. Additionally, individual participants will receive their study results and group allocation information upon the trial’s completion.

### Ethical considerations

The research project protocol has received approval from the Research and Higher Degrees Committee of the Faculty of Medicine, University of Colombo, as well as the Ethics Review Committee of the Faculty of Indigenous Medicine (FIM), University of Colombo. The trial has been registered with the ISRCTN registry under the trial number [ISRCTN64126920—(https://doi.org/10.1186/ISRCTN64126920)]. The study will be conducted in strict adherence to Good Clinical Practice (GCP) guidelines. Any protocol modifications will be submitted to the Ethics Review Committees and updated in the trial registry for approval. Participants will be provided with an information sheet detailing the research in Sinhala, Tamil, and English, and written informed consent will be obtained prior to participation. The information will include the study’s purpose, duration, and potential consequences. Participants will retain the right to withdraw their consent and discontinue participation at any time without any penalty, effect on their medical care, or loss of benefits. The questionnaire will be administered by an interviewer and will remain anonymous. Only essential socio-demographic data, such as occupation and the nature of the participant’s health condition, will be collected. No additional personal data will be gathered by the researchers.

### Data management and ethical oversight

The DSMB will provide independent oversight throughout the trial. Its responsibilities and intervention criteria have been further elaborated in the revised manuscript. Specifically, the DSMB may recommend pausing or terminating the study under the following circumstances:

Safety-related events, including any serious adverse event (SAE) that is judged to be related to the intervention, unexpected patterns of adverse events, or a significant imbalance in safety outcomes between study arms.Recruitment or retention concerns, such as failure to meet predefined recruitment milestones or excessive dropout that threatens scientific validity.Protocol deviations that compromise participant safety or data integrity.Interim data concerns, should any emerging evidence indicate that continuation poses risk or that the trial objectives cannot be achieved.These conditions have now been clearly stated in the ethics section. The long-term data storage plan remains unchanged and aligns with institutional and national guidelines.

### Method of data analysis

For both primary and secondary outcome measures, mean values at baseline and study completion, as well as mean differences, will be compared across the two study arms using ANOVA (Analysis of Variance) or the non-parametric Kruskal–Walli’s test, depending on the data’s normality. Within each treatment arm, changes in primary and secondary outcomes before and after the intervention will be analyzed using either paired-sample *t*-tests or the non-parametric Wilcoxon signed-rank test, based on the distribution of the data. For all normally distributed outcomes, 95% confidence intervals will be calculated. Categorical variables will be analyzed between groups using the Chi-square test. Potential confounding factors will be adjusted using ANCOVA, with adjusted mean values and corresponding confidence intervals subsequently calculated and reported. Regarding missing data, instead of the last observation carried forward, multiple imputation techniques will be employed to handle missing outcome data, ensuring a more robust and unbiased estimation. Statistical analysis will be conducted using the SPSS software (version 20.0), and the level of significance will be set at *α* = 0.05. In cases of missing outcome data, the most recent available values of the outcome measures will be used as replacements. Intention-to-treat analysis will be applied for all efficacy and safety outcomes. Additionally, per-protocol analysis will be conducted for efficacy outcomes, including only participants who complete the follow-up.

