**Study design:**

This two-arm, double blind, placebo-controlled superiority randomized controlled trial evaluates the effects of *Bacopa monnieri* freeze-dried herbal decoction (BMFD) on aging and cognition. Elderly participants (MoCA ≥24) will be randomized to receive BMFD or placebo, administered as 120 mL twice daily for 45 days, with assessments at baseline, 45, and 90 days. Conducted at the Clinical Trial Center, Faculty of Indigenous Medicine, University of Colombo, the trial tests BMFD’s ability to stabilize aging processes and enhance neurocognitive functions.

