### Sample size

The primary outcomes of this clinical trial are telomere length, measured in kilobases using quantitative PCR, and telomerase activity, quantified using an ELISA-based TRAP assay. Both are continuous biological markers that reflect cellular aging processes. Sample size estimation was conducted using the formula for comparing two independent means, appropriate for continuous outcomes. Based on pilot findings reported by Ornish et al. (41), a mean difference of 0.5 kb in telomere length between groups was considered clinically relevant, with a standard deviation (SD) of 0.7 kb. A significance level of *α* = 0.05 and power of 80% (*β* = 0.20) were applied in the calculation. Using these parameters, the required sample size per group was obtained, and after accounting for a 10% dropout rate, the final required sample size was determined to be 37 participants per group, resulting in a total of 74 participants for the study. Although Ornish et al. (41) studied men with prostate cancer—a different population from our healthy older adults—we used this data as it provided the most relevant preliminary estimate of variability and effect size available. We acknowledge that this may limit the precision of our sample size calculation and will interpret our findings accordingly. With a significance level of *α* = 0.05 and power of 80% (*β* = 0.20), the required sample size per group was calculated, and after accounting for a 10% dropout rate, the final sample size was determined to be 37 participants per group, for a total of 74 participants. To further strengthen the validity of these assumptions, a dose-finding and feasibility phase will be conducted prior to the full RCT. Data generated from this phase will be used to validate and refine the expected effect sizes, particularly for telomerase activity and cognitive outcomes, thereby enhancing the robustness of the final trial estimates.

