### Statistical analysis

The statistical analysis plan has been developed to align with the study objectives and ensure rigorous evaluation of outcomes. Descriptive statistics will be used to summarize baseline characteristics across study arms. Continuous primary and secondary outcomes will be assessed for normality prior to analysis. Between-group comparisons of mean changes from baseline to study completion will be conducted using analysis of variance (ANOVA) for normally distributed data or the Kruskal–Wallis test for non-normal data. Within-group pre–post changes will be analyzed using paired-sample *t*-tests or Wilcoxon signed-rank tests, as appropriate.

To account for baseline imbalances and potential confounding factors such as age, sex, and baseline outcome values, analysis of covariance (ANCOVA) will be applied, with adjusted mean differences reported alongside 95% confidence intervals. Categorical variables will be compared between groups using the Chi-square test or Fisher’s exact test, as appropriate.

Missing outcome data will be handled using multiple imputation methods to minimize bias and improve the robustness of estimates. The primary analysis will follow the intention-to-treat principle for all efficacy and safety outcomes, with a secondary per-protocol analysis conducted for efficacy outcomes among participants who complete the follow-up assessments. All statistical analyses will be performed using SPSS software (version 20.0), with a two-sided significance level set at *α* = 0.05.

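### Paired tests within each arm are planned at alpha 0.05 beside the valid between-arm comparisons, with no statement that only the latter decide efficacy

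*Protocol article*

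**What the plan says.** Two sections of the protocol article describe the analysis.

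- **Method of data analysis** first compares the two arms by ANOVA or Kruskal–Wallis, then adds: "Within each treatment arm, changes in primary and secondary outcomes before and after the intervention will be analyzed using either paired-sample" t-tests or Wilcoxon signed-rank tests. It also plans ANCOVA for confounders.
- **Statistical analysis** again puts the comparison of arms first: "Between-group comparisons of mean changes from baseline to study completion will be conducted using analysis of variance (ANOVA"), with Kruskal–Wallis as the alternative. It then says: "Within-group pre–post changes will be analyzed using paired-sample" t-tests or Wilcoxon tests. ANCOVA follows, with baseline outcome values among the covariates, "with adjusted mean differences reported alongside 95% confidence intervals". All analyses are run "with a two-sided significance level set at" 0.05.

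The within-arm tests cover all primary and secondary outcomes. Neither section calls them descriptive, and neither names the test on which efficacy will be judged. The Sample size section rests on a between-group difference.

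**The concern.** The trial asks whether BMFD differs from placebo. A paired test inside the BMFD arm asks whether that arm changed from baseline. Anything that moves both arms makes its null hypothesis false even when BMFD and placebo are identical.

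Shared movement is plausible here. Table 2 has MoCA at baseline, Week 6 and Week 12, so a practice gain is possible. Telomere and telomerase samples are taken twelve weeks apart. Drift in either direction can mislead, because the abstract gives the aim as testing BMFD's "ability to stabilize aging processes and enhance neurocognitive functions". With upward drift, a significant gain under BMFD but not under placebo could be read as enhancement. With downward drift, a significant loss under placebo but not under BMFD could be read as stabilisation. Neither pattern tests the difference between arms.

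At stake is a set of p-values, two per outcome, that make no use of the randomised control but are reported at the same alpha as the comparisons that do.

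**Working it through.** **The plan's own figure.** The Sample size section uses "a mean difference of 0.5 kb in telomere length between groups was considered clinically relevant", "with a standard deviation (SD) of 0.7 kb", two-sided alpha 0.05 and 80% power.

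- Normal approximation: n = 2 × (1.960 + 0.842)² × 0.7² / 0.5² = 30.8, so 31 per arm; 31 / 0.9 = 34.4, so 35 with 10% dropout.
- t-based version: 32 per arm; 32 / 0.9 = 35.6, so 36.

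The stated 37 per arm is within two of both. The trial is therefore sized for a comparison between arms, and the point below does not alter that size.

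**Inputs for the check**

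- Completers per arm: 37 × 0.9 = 33.3, taken as 33.
- Treatment effect: none (inert BMFD).
- Shared drift d, in SDs of the individual change, equal in both arms. **This is an assumption**: the documents give no drift for any outcome, so a range is shown.

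**Formulas**

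- Within-arm rejection probability p: the paired t statistic follows a noncentral t distribution with n − 1 = 32 df and noncentrality d√33 = 5.745d. The test rejects when |t| exceeds the 97.5% point of t with 32 df.
- Significant improvement with BMFD but no significance with placebo: u × (1 − p), where u is the upper-tail part of p and the arms are independent.
- Between-arm t-test on the same changes: 100,000 simulated trials at each of d = 0, 0.2, 0.34, 0.5 and 0.8.

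**Results, 33 per arm, inert BMFD**

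| Assumed drift d | BMFD-arm test rejects | BMFD significant, placebo not | Between-arm test rejects (simulated) |
|---|---|---|---|
| 0 | 5.0% | 2.4% | 5.0% |
| 0.1 | 8.6% | 7.3% | – |
| 0.2 | 20.0% | 15.9% | 4.9% |
| 0.3 | 38.7% | 23.7% | – |
| 0.34 (simulated) | 47.4% | 25.1% | 4.9% |
| 0.4 | 60.6% | 23.9% | – |
| 0.5 | 79.5% | 16.3% | 5.0% |
| 0.8 | 99.4% | 0.6% | 5.0% |

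With all 37 per arm retained, the within-arm rejection rates at d = 0.1, 0.2, 0.3 and 0.5 are 9.1%, 22.0%, 42.7% and 84.1%.

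The misleading pattern peaks at about 25% because p(1 − p) is largest at p = 0.5. The arms are exchangeable, so placebo significant and BMFD not is equally likely. For large drift both arms are usually significant: at d = 0.5 this happens in 0.795² = 63% of trials, which itself points to drift.

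**The case against.** A reader might infer that the plan will judge efficacy from the before-after tests, so that an inert BMFD would be declared effective. The documents do not support this. Both analysis sections put the between-arm comparison first and add ANCOVA, the Statistical analysis section names baseline values as covariates, and the sample size rests on a difference between groups. These comparisons cancel shared drift. Nothing says that efficacy will be concluded from a within-arm p-value. The abstract's words about enhancing function state an aim within a placebo-controlled design, not an analysis rule.

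Other objections also carry weight:

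- The drift is assumed in size and direction. At d = 0.1 the inflation is modest (8.6%). MoCA is a secondary outcome, and the assay section describes calibration and checks of inter-assay variability that should limit laboratory drift.
- A statistical analysis plan may exist, and ranking tests as confirmatory or supportive is commonly left to it. Silence on the ranking would not be a fault by itself.
- Replacing the paired t-test by a within-arm 95% CI would change little, since that interval excludes zero exactly when p < 0.05.

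What remains does not depend on silence alone. The article states an inferential analysis for every outcome, at the same alpha, that does not test the trial's question, and it sets this unranked beside the analysis that does.

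**Conclusion.** The point holds as one of interpretation and reporting, of minor to moderate severity. The between-arm comparison, its 5% error rate and the sample size are not affected. The within-arm tests cannot show an effect of BMFD against placebo. For an inert product with 33 completers per arm, they reject in about 9% to 80% of trials as the assumed shared drift goes from 0.1 to 0.5 SD of change, and significance in BMFD alone arises in at most about 25%. These figures hold only under equal drift in both arms, independent and roughly normal changes, and a drift size that the documents do not supply. Harm follows only if within-arm p-values are read as evidence of efficacy, and the text as written leaves that reading open.

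**What to change.** In both Method of data analysis and Statistical analysis:

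1. Delete the within-arm paired t-tests and Wilcoxon signed-rank tests.
2. Report within-arm change descriptively, for example as mean and SD by arm and visit.
3. State that every efficacy conclusion rests only on the baseline-adjusted BMFD-placebo difference from ANCOVA, with its 95% CI.

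The third item does most of the work. The cost is a change of wording in two sections and the loss of the within-arm p-values. No data, visits or participants are added.

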## Discussion

As per modern science, aging is the time-dependent, physiological decline of biological processes that are often associated with age-related diseases. Those pathologies often associated with aging, such as cellular inflammation and atherosclerosis, involve hyperactivity or uncontrolled cellular growth. There are about nine hallmarks of aging: genomic instability, telomere attrition, epigenetic alteration, loss of proteostasis, deregulated nutrient sensing, mitochondrial dysfunction, cellular senescence, stem cell exhaustion, and altered intracellular communication (49). The hallmark of anti-aging action is calorie restriction (CR), which involves the extension of the life span and the suppression of age-related diseases. Calorie restriction mechanisms play a major role in modulating chronic inflammation at the molecular level, the impact of epigenetic chromatin and histone modification, and the ultimate control of gene expression (50). Changes in telomere length and telomerase activity could provide valuable insights into the potential influence of *Bacopa monnieri* on aging-related processes. Since telomere shortening is a hallmark of cellular aging and genomic instability, any modulation in its length may indicate an impact on biological aging. Similarly, alterations in telomerase activity could reflect the extent to which *Bacopa monnieri* influences cellular longevity and regenerative capacity. Investigating these changes will help determine whether *Bacopa monnieri* plays a role in slowing down aging-related cellular decline or enhancing genome stability.

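### Uncontrolled before-after significance tests within each arm are planned for the primary and secondary outcomes at the same 0.05 level as the comparison with placebo, and are not marked as descriptive

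*Protocol article*

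**What the plan says.** Two sections of the protocol article describe the analysis, and both include within-arm tests.

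- **Method of data analysis:** "Within each treatment arm, changes in primary and secondary outcomes before and after the intervention will be analyzed using either" paired-sample t-tests or the Wilcoxon signed-rank test, depending on the distribution.
- **Statistical analysis:** "Within-group pre–post changes will be analyzed using paired-sample" t-tests "or Wilcoxon signed-rank tests, as appropriate". All analyses are run "with a two-sided significance level set at" 0.05.

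Neither section calls the within-arm tests descriptive, supportive or exploratory. Neither says which analysis carries the conclusion about BMFD.

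Both sections also plan between-arm comparisons by ANOVA or Kruskal-Wallis, and both name them before the within-arm tests. Both add ANCOVA. In the Statistical analysis section, "analysis of covariance (ANCOVA) will be applied, with adjusted mean differences reported alongside 95% confidence intervals", and baseline outcome values are among the covariates named. The Sample size section is likewise built on a comparison of arms: "a mean difference of 0.5 kb in telomere length between groups was considered clinically relevant".

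**The concern.** A paired test in the BMFD arm asks whether that arm changed. It does not ask whether BMFD changed it, and it sets aside the placebo arm that the trial was built to provide. Three sources of change common to both arms are plausible from the article itself:

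- **Practice.** Table 2 has the MoCA given at baseline, week 6 and week 12.
- **Placebo response.** Quality of life is a questionnaire outcome, and both arms prepare and drink a decoction every day.
- **Assay variation between runs.** The telomere and telomerase section plans to evaluate intra- and inter-assay variability. The article does not say that a participant's baseline and later samples share a run.

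If such tests are reported in pairs, a significant change in BMFD beside a non-significant one in placebo is easily taken for a treatment effect. It is not a test of BMFD against placebo. Because the within-arm tests cover the primary as well as the secondary outcomes, the opening for that misreading exists on every outcome.

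**Working it through.** **Inputs from the article.** Difference 0.5 kb, SD 0.7 kb, alpha 0.05, power 80%, dropout 10%, 37 per group (Sample size); two-sided 0.05 (Statistical analysis); 1:1 allocation (Randomization).

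**Input assumed.** A shift common to both arms of d standard deviations of the change. The article gives no such figure, so a range is shown.

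**1. The plan's own figure.** n per arm = 2 × (1.960 + 0.842)² × 0.7² / 0.5² = 30.8, rounded up to 31. After 10% dropout, 31 / 0.9 = 34.4, rounded up to 35. The t-based version gives 32 per arm, and 32 / 0.9 = 35.6, rounded up to 36. The stated 37 is within two of either, so the sample size broadly reproduces. It rests on a difference between arms, not on change within one arm.

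**2. Completers.** 37 × 0.9 = 33.3, taken as 33 per arm.

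**3. Within-arm test with no BMFD effect.** For a two-sided paired t-test at 0.05 with n = 33, the chance of a significant rise is p = 1 − F(t₀.₉₇₅,₃₂), where F is the noncentral t distribution function with 32 degrees of freedom and noncentrality d√33. The arms are independent and share the same d. So the chance of a significant rise in BMFD and none in placebo is p(1 − p).

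| Common shift d (assumed) | p: significant rise in BMFD | p(1 − p): rise in BMFD, none in placebo |
|---|---|---|
| 0 | 0.025 | 0.024 |
| 0.1 | 0.080 | 0.074 |
| 0.2 | 0.199 | 0.159 |
| 0.3 | 0.387 | 0.237 |
| 0.35 | 0.496 | 0.250 |
| 0.4 | 0.606 | 0.239 |
| 0.5 | 0.795 | 0.163 |

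p(1 − p) cannot exceed 0.25. It reaches that value when p is one half, here near d = 0.35.

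**4. Between-arm test under the same conditions.** In 100,000 simulated trials per setting, with 33 per arm and the same shift in both arms, the two-sided between-arm t-test rejected in 5.0% of trials at d = 0, 4.9% at d = 0.3 and 4.9% at d = 0.5. The common shift cancels.

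**The case against.** The strongest reply is that nothing in the article draws an efficacy conclusion from a within-arm result. The between-arm comparison comes first in both analysis sections, ANCOVA follows, the sample size rests on a between-group difference, and the trial is framed throughout as BMFD against placebo. This stands, and it makes the flaw secondary. A reader might infer that efficacy will be judged on the before-after tests; the article does not say so. What remains is that it plans these tests at the same level and does not bar that use.

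Four other points from the same side:

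- **Regression to the mean.** A reader might add it to the list of common shifts because entry depends on the MoCA. Entry at 24 or above selects high scores, so the expected regression is downward. It would hide a MoCA gain, not credit one to BMFD, and it has no place in this point.
- **Assay safeguards.** The article plans internal controls, calibration, standard curves, repeat criteria and coded samples. These limit run-to-run variation, though they may not remove it. For telomere length, practice is irrelevant and the Discussion describes the natural course as a decline, so a large upward common shift has no support there.
- **The Discussion.** The sentence "any modulation in its length may indicate an impact on biological aging" might be read as showing how the within-arm results will be interpreted. It explains why the marker was chosen and names no arm, test or p-value, so it is not evidence of a planned misreading.
- **An analysis plan not shown.** A rule on interpretation may be written there. That is possible, but the point rests on tests that the article states twice, not on an omitted detail.

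**Conclusion.** The point holds as a secondary flaw in a stated analysis. Within-arm tests on the primary and secondary outcomes share the two-sided 0.05 level with the comparison that answers the trial's question, and nothing marks them as descriptive. They cannot separate BMFD from change common to both arms.

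The size is illustrative. With no BMFD effect, 33 completers per arm and an assumed common shift of 0.1 to 0.5 SD of change, a significant rise in BMFD without one in placebo appears in about 7% to 25% of trials per outcome, against 2.4% with no shift. The between-arm test stays near 5%. It would be tempting to say that the error is ten times too high. That ratio (0.250 / 0.024) is the peak over assumed shifts; at d = 0.1 it is about three (0.074 / 0.024). The base also counts rises only, whereas counting changes in either direction gives 4.8% with no shift. The documents do not say which shift, if any, applies to which outcome.

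**What to change.** In both Method of data analysis and Statistical analysis:

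1. Remove the paired t-tests and Wilcoxon signed-rank tests within arms.
2. Report within-arm change descriptively, as mean or median change with its spread. If a confidence interval is shown, say that it is not used for inference. For a paired t-test, a 95% CI that excludes zero is the same event as p < 0.05, so replacing one with the other would not help on its own.
3. Add one sentence: conclusions about BMFD rest only on the between-arm comparison, using the baseline-adjusted ANCOVA difference with its 95% CI, which is already planned.

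The third item does most of the work. The change costs a few sentences and leaves sample size, visits and data untouched. The downside is fewer p-values to report.
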